## Methods/design

The main objective of this study is to develop, implement, and assess the effectiveness of the mobile SMS counselling intervention to improve the knowledge, attitude, and practices of HIV/AIDS patients concerning HIV/AIDS prevention in Malaysia. The specific objectives are given below: to assess the patients initial response to mobile SMS counselling intervention in terms of acceptability, feasibility, and sustainability; to develop mobile SMS counselling intervention for HIV/AIDS prevention; to identify factors associated with the willingness to read text messages on HIV/AIDS prevention in Malaysia; to determine the socio-demographic and environmental factors, level of knowledge, attitude, and practices of patients on HIV/AIDS prevention; to develop and implement a Mobile SMS counselling HIV/AIDS prevention intervention to improve the knowledge, attitude, and practices of HIV/AIDS patients; to determine the association among the socio-demographic factors and environmental factors with knowledge, attitude, and practices of HIV/AIDS patients about HIV/AIDS prevention at the baseline and post intervention; to compare the mean scores for knowledge, attitude, and practices among HIV/AIDS patients between the intervention and the control group at the baseline and post intervention (within group and between groups); and to evaluate the effectiveness of Mobile SMS counselling intervention among HIV/AIDS patients to improve the knowledge, attitude, and practices concerning HIV/AIDS.

The hypotheses are given below: There is an association between the willingness to read text messages and HIV/AIDS patients in Malaysia; there is no significance in the socio-demographic and environmental factors, level of knowledge, attitude, and practice of patients concerning HIV/AIDS prevention; there is an association between the social-demographic and environmental factors, and the knowledge, attitude, and practices of HIV/AIDS patients concerning HIV/AIDS prevention at baseline and post-intervention; there is a significant difference in the mean scores for the knowledge, attitude, and practices of HIV/AIDS patients between the intervention and control group at the baseline and post-intervention (within and between groups), and the application of Mobile SMS counselling intervention to improve the impact of the HIV/AIDS prevention knowledge, attitude, and practices among patients, between the intervention and the control group.

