The research questions are given below: What are the socio-demographic and environmental factors associated with the knowledge, attitude, and practice of HIV/AIDS patients? What is the difference in the mean scores for the knowledge, attitude, and practices of HIV/AIDS patients concerning HIV/AIDS prevention for the intervention and control groups? And what is the impact of Mobile SMS counselling intervention on the knowledge, attitude, and practices of HIV/AIDS patients?

This is a mixed methods research. The first phase will be a qualitative study to develop a mobile SMS counselling intervention concerning the knowledge, attitude, and practices of patients concerning HIV/AIDS prevention, while the second phase will be a quantitative study to implement and evaluate the effectiveness of a mobile-based counselling intervention concerning the knowledge, attitude, and practices of patients in respect of HIV/AIDS prevention. Three focus group discussions (FGDs) will be conducted with 6 male HIV/AIDS patients with FGDs, 6 female HIV/AIDS patients with FGDs, 10 community leaders from a village with FGDs, and three in-depth interviews (IDIs) will be conducted with 3 HIV/AIDS patients. The second phase, the cluster randomized clinical trial, will be carried out for approximately 12 months from September 2019 to July 2020. The hospital/NGOs (or cluster) will be the unit of randomization, and an equal number of hospitals/NGOs will be randomized to one of the two arms. This phase includes a Community trial and pre- and post-assessment through face-to-face interviews using a semi-structured questionnaire (Fig. 1). The study population will be HIV/AIDS patients in the Kuala Terengganu and Kuala Nerus districts of Malaysia. A complete list of HIV/AIDS patient registration will be collected from the Hospitals/NGOs in Kuala Terengganu and Kuala Nerus districts from January 2018 to March 2019. The sampling units will be individual patients who are admitted into the Hospital/NGOs between January 2018 and March 2019 and who are eligible according to the inclusion criteria for this study. The criteria for inclusion in this study include all persons diagnosed with HIV ≥ 18 years of age. Patients excluded from this study are those patients who are HIV positive but diagnosed with psychiatric disorders and are mentally incapacitated. The sample size estimation formula for hypothesis testing of the two-group comparison is used [13]:

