**Fig. 1 Fig1:**
[figure not shown]
Study flow diagram showing the key components of the intervention

### N = 87

Where P1 = HIV Prevalence in 2012 = 0.189 & P2 = HIV Prevalence in 2014 = 0.163 [2]. P̃ = (P1 + P2)/2 = 0.176. Z1 – α/2 = standard error when α = 0.05 (95% confidence interval) = 1.96, and Z1 – β = standard error associated with power = 0.842 (β = 0.20) and Power (1 – β) = 80%.

As participants are nested within in villages, a potential design effect needs to be considered. The assumed number of participants per hospital/NGOs is 20, and an intra-cluster correlation coefficient of 0.05 can be expected. This would result in a design effect = 1 + (m-1) × ICC = 1 + (20–1) × 0.05 = 2. Based on the above formula, the required minimum sample size for each group, n is **174.** To factorise in 10% attrition (32), the total required per group is **192**; hence, a total of **384** patients will be required for the sample in both groups.

Figure 2 below shows a schematic diagram for the development of the intervention module used in this study. The module will be developed through the process of consultation with a group of experts who will include one professor of statistics, one expert in behavioural intervention, one senior medical doctor, and one HIV/AIDS specialist (Fig. 2). The mobile based SMS counselling intervention aims to increase the knowledge, attitude, and practices of patients concerning HIV/AIDS prevention in Malaysia. The SMS will be developed by the researcher based on FGDs and a literature review. It uses informal language and will be sent weekly on Friday, which is a holiday. These factors have been shown to have an impact and positively affect the message acceptability when using SMSs for sexual health promotion [14, 15]. Mobile phones and the Internet are popular everywhere in Malaysia, and are well-liked by people, so the study aims to determine whether they would be effective and improve patient’s knowledge, attitude, and practices concerning HIV/AIDS prevention.

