**Fig. 2 Fig2:**
[figure not shown]
Schematic diagram of the development of the intervention module

The control group patients will not receive any SMS during the study periods, but the usual information received from the mass media (newspaper, TV, Radio) or any campaign for HIV/AIDS prevention. However, they will receive the SMS counselling intervention about HIV/AIDS after data collection.

The Statistical Package for Social Science (SPSS) version 22 will be used to analyse the data. Data will be collected, checked, cleaned, and data entry will be conducted carefully and successfully. Factors with a statistically significant association with the socio-demographic and environmental variables on HIV/AIDS prevention knowledge, attitude, and practices will be identified at the baseline, immediate post intervention, and after 3 months follow up in the logistic model (ρ-value of 0.05) controlling for other variables. To determine the significant difference between the intervention and the control groups, a t-test and chi-square test will be used. To identify the impact of two different interventions, 2-way repeated measure ANOVA and one-way ANOVA will be used.

The main findings are given below: development of mobile SMS based counselling intervention for prevention of HIV/AIDS with FGDs; identification of implementation process for mobile SMS based counselling intervention for prevention of HIV/AIDS patients; development of tools for measuring the effectiveness of Mobile SMS based counselling intervention for prevention of HIV/AIDS patients; development of an effective intervention for HIV/AIDS patients in a low resource setting to improve the knowledge, attitude, and practices concerning HIV/AIDS prevention, and assessment of the effectiveness of a mobile SMS based counselling intervention programme on the HIV/AIDS prevention knowledge, attitude, and practices of HIV/AIDS patients.

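### A logistic model is fixed for the factors associated with knowledge, attitude and practice, although these outcomes are defined as scores, so categorising them would lose information the trial collects

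*Protocol article*

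**What the plan says.** All references are to the Methods/design section of the protocol article.

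- **Outcome scale.** One specific objective is "to compare the mean scores for knowledge, attitude, and practices among HIV/AIDS patients between the intervention and the control group". The research questions use the same scale: "What is the difference in the mean scores for the knowledge, attitude, and practices of HIV/AIDS patients".
- **Association aim.** A separate objective is "to determine the association among the socio-demographic factors and environmental factors with knowledge, attitude, and practices of HIV/AIDS patients", at baseline and after the intervention. A matching hypothesis and the opening research question repeat it.
- **Model for the association aim.** The statistical analysis paragraph (after Fig. 2) says that the associated factors "will be identified at the baseline, immediate post intervention, and after 3 months follow up in the logistic model", adjusted for other variables and judged at 0.05.
- **Analyses of the arms.** For the difference between groups, "a t-test and chi-square test will be used". For the impact of the intervention, "2-way repeated measure ANOVA and one-way ANOVA will be used".
- **A hint of categories.** Another objective speaks of the "level of knowledge, attitude, and practices of patients on HIV/AIDS prevention".

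The article does not say whether the logistic model is binary or ordinal.

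**The concern.** The same three outcomes appear in two forms. In the objectives, the research questions and the arm comparison they are scores with means. In the analysis of associated factors they enter a logistic model, which cannot take a score as its outcome unless the score is first grouped.

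The article itself fixes this choice, so an analysis plan that follows it would keep the less efficient method. The absence of a cut-off is not the complaint, since that detail may sit in a fuller document. The point is that modelling the collected score directly would usually be better than any coarse grouping of it.

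At stake is the power to detect associated factors, and the stability of the list of factors that reach 0.05, because both depend on where the score is cut.

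**Working it through.** The article gives no figure for the efficiency or power of the association analyses, so there is none to reproduce. Its 80% power belongs to a sample size calculation for two proportions (0.189 and 0.163), which is a separate matter. Below, 80% is only a reference level.

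**Inputs from the article.** Two-sided 5% level, given as "standard error when α = 0.05 (95% confidence interval) = 1.96"; 0.842 for 80% power; 384 patients in total; 2 × 174 = 348 before the attrition allowance.

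**Assumptions.** An approximately normal score, modest effects and independent patients. The cut-points are illustrative.

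**1. Score split in two.** With a proportion q on one side of the cut, the information kept relative to the mean of the score is φ(z_q)² / [q(1 − q)]. At the median this is 0.3989² / 0.25 = 0.637, which equals 2/π. Power becomes Φ(2.802 × √kept − 1.96), where 2.802 = 1.96 + 0.842.

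| Split | Information kept | Lost | Power, if 80% on the score |
|---|---|---|---|
| 50/50 | 63.7% | 36.3% | 61% |
| 70/30 | 57.6% | 42.4% | 57% |
| 80/20 | 49.0% | 51.0% | 50% |

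For the median split: 2.802 × √0.637 − 1.96 = 0.276, and Φ(0.276) = 0.609. The median is the most favourable cut, so under normality the loss is at least 36.3%. In patients, 384 × 0.637 ≈ 244 and 348 × 0.637 ≈ 222.

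**2. Check by simulation.** The setting was a balanced two-level factor with 192 patients per level and a standardised difference of 0.286, in 1,500 simulated data sets. Power was 80% for linear regression on the score and 64% for logistic regression after a split at the sample median. The formula for two proportions gives 61%.

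**3. Ordinal logistic model.** With k equal categories of a normal score, the information kept is k × Σ(φ_upper − φ_lower)², where the two terms are the normal densities at the limits of each category.

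| k | Kept | Lost |
|---|---|---|
| 3 | 79.3% | 21% |
| 4 | 86.1% | 14% |
| 5 | 89.7% | 10% |
| 10 | 95.9% | 4% |

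**4. Other score shapes, split in two.** The general form is f(c)²σ² / [q(1 − q)], where f is the density at the cut c and σ² the variance.

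- Logistic-shaped score: 82.2% kept at the median, so 18% is lost.
- Uniform score: 33.3% kept at the median (67% lost), but 92.6% at a 10/90 split.
- Laplace score (sharply peaked, heavy tails): the ratio at the median is 2.0, so a median split loses nothing against the mean.

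The size of the loss therefore depends on both the model and the score distribution.

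**The case against.** Several points can fairly be made for the plan.

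- **A reader might infer that the scores must be split in two.** The article does not say so. It names a logistic model without its type. The objective on level and the chi-square test suggest that a categorised version may be planned alongside the score. An ordinal model fits the wording and loses less. This stands: the binary figures hold only if the split is binary.
- **A reader might infer that a third or more of the information is lost in any case.** That needs a roughly normal score and a binary cut. The article gives no range, standard deviation or distribution for the scores. This stands too.
- **The power figures are not the plan's.** No power is stated for the associations, so the fall from 80% to 61% only illustrates the scale of the loss.
- **A reader might infer that the effectiveness result is weakened.** It is not. Group differences and the impact of the intervention go to other methods, and the t-test and ANOVA keep the score.
- **Odds ratios for factors beside mean differences for arms might look inconsistent.** They answer different questions, and reporting both is not an error. Logistic regression on a categorised level is valid, though less efficient.

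These points limit the size and reach of the concern. They do not remove the mismatch between the defined scale and the named model, and they give no reason to prefer grouping a score that is already collected.

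**Conclusion.** The point holds in a limited form. The article names a model that needs a categorised outcome for three outcomes that it defines as scores, and grouping would in general lose information.

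Under approximate normality the loss is at least about 36% for a binary split and about 14–21% for an ordinal model with four or three equal categories. The actual loss cannot be fixed from the article, because neither the type of logistic model nor the score distributions are given.

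The effect is confined to the association objective, its hypothesis and its research question. It makes that analysis less efficient, not invalid, so this is a cheap improvement and not a threat to the trial's main conclusion.

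**What to change.** In the statistical analysis paragraph, replace the logistic model with a linear mixed model of each knowledge, attitude and practice score on the socio-demographic and environmental factors:

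- a random intercept for hospital/NGO, so that the model carries the clustering for which the sample size section assumes an intra-cluster correlation of 0.05;
- study arm as a covariate at the two post-intervention times;
- either a separate fit at each time point, or one joint model with a patient-level random effect and a time term;
- adjusted mean differences with 95% confidence intervals.

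If a good/poor category is wanted for readers, keep it as a descriptive secondary table with the cut-off fixed in advance.

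The cost is a change of analysis wording. No new data are needed, and SPSS, the named software, fits these models. The small downside is that results appear as mean differences and not as odds ratios.

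### Hospitals/NGOs are randomised, but every named between-arm test treats patients as independent; at the plan's own ICC a single-visit comparison has about 16% type I error, not 5%

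*Protocol article*

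**What the plan says.** Methods/design in the protocol article sets up a cluster trial: "The hospital/NGOs (or cluster) will be the unit of randomization", and "an equal number of hospitals/NGOs will be randomized to one of the two arms". The sample size paragraph, after Fig. 1, recognises the clustering. It states: "The assumed number of participants per hospital/NGOs is 20, and an intra-cluster correlation coefficient of 0.05 can be expected". It then computes: "This would result in a design effect = 1 + (m-1) × ICC = 1 + (20–1) × 0.05 = 2". On that basis 87 per group becomes 174, and 192 after attrition.

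The analysis paragraph, after Fig. 2, names the comparisons of the arms. One sentence reads: "To determine the significant difference between the intervention and the control groups, a t-test and chi-square test will be used". The next reads: "To identify the impact of two different interventions, 2-way repeated measure ANOVA and one-way ANOVA will be used". A logistic model is also planned, but for associations with socio-demographic and environmental factors, not for the arm comparison. The article nowhere mentions a cluster term, a mixed model, GEE, cluster-robust standard errors or a cluster-level analysis.

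The Abstract (Results) defines the main outcomes as differences in knowledge, attitude and practices between baseline and two later assessments: immediately after the intervention and after 3 months.

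**The concern.** The four named tests, in their ordinary form, take the patient as the independent unit. Patients of the same hospital/NGO share staff, case mix and local campaigns, and they are allocated together. The plan accepts this when it sizes the trial and drops it when it tests.

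If the ICC is positive, the patient-level standard error of an arm difference at a visit is too small, its confidence interval too narrow and its p-value too low. A significant difference between arms could then reflect nothing more than differences between hospitals/NGOs. The trial's purpose is to show effectiveness, and the Discussion expects the results to influence decisions and to be taken up elsewhere, so the false-positive rate of the arm comparison matters.

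**Working it through.** **Inputs.** From the sample size paragraph: m = 20 patients per hospital/NGO, ICC = 0.05, two-sided alpha 0.05 (z = 1.96), 87 per group before the design effect. The number of clusters is not stated; 192/20 = 9.6 implies about 10 per arm.

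**Reproducing the plan's figures.** DE = 1 + (20 − 1) × 0.05 = 1.95, rounded in the article to 2. Then 87 × 2 = 174, 174 × 1.10 = 191.4, rounded up to 192, and 2 × 192 = 384. These steps reproduce. The derivation of 87 is a separate matter and does not enter the calculation below, which depends only on the design effect.

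**Single-visit comparison (t-test, chi-square test, one-way ANOVA).** The true standard error is √1.95 = 1.40 times the one that the test uses. The actual two-sided error is therefore

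2 × [1 − Φ(1.96/√DE)] = 2 × [1 − Φ(1.96/1.396)] = 0.160,

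which is 3.2 times nominal. With the article's rounded DE of 2 it is 0.166.

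| Patients per cluster | ICC | DE | Actual error |
|---|---|---|---|
| 20 | 0.05 (plan) | 1.95 | 0.160 |
| 18 (after 10% attrition) | 0.05 | 1.85 | 0.150 |
| 17 | 0.05 | 1.80 | 0.144 |
| 20 | 0.02 (assumed) | 1.38 | 0.095 |
| 20 | 0.10 (assumed) | 2.90 | 0.250 |
| 48 (assumed, 4 clusters per arm) | 0.05 | 3.35 | 0.284 |

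A simulation of 20,000 null trials with 10 clusters of 20 per arm and ICC 0.05 agrees: t-test 0.157, chi-square test 0.164 to 0.168. A t-test on cluster means of the same simulated data gives 0.048.

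**Group-by-time test (two-way repeated measures ANOVA).** A cluster effect that is constant over time cancels from a within-patient change, so what matters is the ICC of the change. The article does not give it. Let the correlation of a cluster's effect between visits (cluster autocorrelation) be c, and assume that half of the within-cluster variance is stable within patients. For a change between two visits,

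ICC of change = 0.05(1 − c) / [0.05(1 − c) + 0.95 × 0.5].

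At 17 patients per cluster:
- c = 1.0: ICC 0, DE 1.00, error 5%.
- c = 0.8: 0.010/0.485 = 0.0206, DE 1.33, error 8.9%.
- c = 0.5: 0.025/0.500 = 0.05, DE 1.80, error 14.4%.

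Simulating the three-visit group-by-time F test (20 clusters of 17 in all, ICC 0.05) gave about 5%, 11% and 18% in these three cases. A t-test on cluster-mean change stayed at about 5% throughout.

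**Does the larger sample help?** The error formula contains m and ICC but not the number of patients. Enrolling 384 rather than fewer, in clusters of 20, leaves the 16% unchanged.

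**The case against.** The strongest defence is that the outcome is defined as change from baseline and that the impact of the intervention is assigned to the repeated measures ANOVA. The natural test there is group-by-time, and stable differences between hospitals/NGOs cancel from it. This stands as a limit on the size of the problem. A reader might infer that the false-positive rate is tripled for every listed test, including this one. The documents do not support that, because they give neither an ICC for change nor any statement on how stable cluster effects are. It does not rescue the plan: the article assigns the difference between groups to the t-test and chi-square test, and it does not justify constant cluster effects.

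A second defence is that a fuller protocol or SAP may handle clustering. That would be fair had the article left the tests open. It names them, so a later document would have to contradict it.

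A third point concerns the sentence "As participants are nested within in villages, a potential design effect needs to be considered". One might read it as showing that a different unit was used for the sizing. The sentence that follows it uses hospital/NGO, as does the design text, and no calculation changes. It is a wording slip to tidy and adds no weight.

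**Conclusion.** The concern holds within these limits. The named between-arm tests conflict with the unit of randomisation and with the plan's own design effect.

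- **Single-visit comparisons:** type I error is about 16% at the stated cluster size and ICC, and about 14 to 15% after attrition. This rests on figures in the article and on roughly equal clusters.
- **Group-by-time test:** from 5% (no inflation) to roughly three times nominal, for assumed cluster autocorrelations from 1.0 down to 0.5. These autocorrelations and the within-patient correlation are assumptions, not figures from the article.
- **Other ICCs and cluster counts:** the ICC range of 0.02 to 0.10 and the case of few, large clusters are also assumptions. They show direction and scale only.

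The analysis text should be corrected before the arms are compared, because it governs the trial's main conclusion and can be changed without touching design or data collection.

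**What to change.** Replace the listed arm comparisons with an analysis that respects the randomised hospital/NGO:

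- **Scores:** a linear mixed model on the two post-baseline assessments, with arm, visit, arm-by-visit and baseline score as a covariate (baseline not also entered as an outcome row). Include random effects for hospital/NGO, hospital/NGO-by-visit and patient, with Satterthwaite degrees of freedom. The hospital/NGO-by-visit term is needed: in balanced data a model with random intercepts for hospital/NGO and patient alone leaves the arm-by-visit inflation in place.
- **Binary items:** the logistic mixed equivalent.
- **Few clusters:** make a t-test on hospital/NGO mean change, or on baseline-adjusted hospital/NGO means, the main analysis, with K − 2 degrees of freedom for K clusters.
- **Reporting:** state the number of clusters and the estimated ICC, and name hospital/NGO as the nesting unit throughout.

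The cost is revised wording and a little programming. Single-visit confidence intervals become about 1.4 to 1.5 times wider: √1.95 = 1.40 from the design effect and, with 20 clusters and 18 degrees of freedom, 1.40 × 2.10/1.96 = 1.50. That is their correct width.

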**Results:**

The main outcomes of this study will be the differences in knowledge, attitude, and practices of patients concerning the prevention of HIV/AIDS between the baseline and immediate follow-up after the intervention, and after 3 months.

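### None of the tests named for the arm effect adjusts for the baseline score that the trial already collects, so precision is given up that a change of analysis wording would recover

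*Protocol article*

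**What the plan says.** The design is a cluster-randomised comparison of SMS counselling with no SMS. Scores come from "pre- and post-assessment through face-to-face interviews using a semi-structured questionnaire" (Methods/design). The Abstract (Results) gives the main outcomes as differences in knowledge, attitude and practices "between the baseline and immediate follow-up after the intervention, and after 3 months", which makes three time points. The objectives in Methods/design compare mean scores "between the intervention and the control group at the baseline and post intervention (within group and between groups").

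The analysis paragraph after Fig. 2 names the tests of the arm effect:
- For comparing the two arms it gives the t-test and the chi-square test, without saying which quantity each is run on.
- For the effect of the intervention it says: "To identify the impact of two different interventions, 2-way repeated measure ANOVA and one-way ANOVA will be used".

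The only model there with covariates is a logistic one ("after 3 months follow up in the logistic model"). It is meant to find socio-demographic and environmental factors associated with the outcomes and is not given as the test of the intervention. Software is covered by one sentence: "The Statistical Package for Social Science (SPSS) version 22 will be used to analyse the data". No procedure within it is named.

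**The concern.** A pre-treatment measurement of the outcome is usually the strongest predictor of the follow-up measurement. Using it as a covariate removes outcome variation that has nothing to do with the intervention. None of the named tests does so.

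- **t-test and one-way ANOVA.** Run on follow-up scores, they leave baseline out altogether. Any chance baseline difference between arms then stays in the estimate. At 20 patients per hospital/NGO, 384 patients make only about 19 clusters (384/20 = 19.2), so such differences are a realistic prospect.
- **Two-way repeated-measures ANOVA.** The Abstract and the objectives treat baseline as one of the compared time points, so baseline is most naturally a level of the repeated factor. The group-by-time term then uses it as change from baseline, which is less efficient than covariate adjustment.

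What is at stake is precision, and some protection against chance imbalance. It is not the validity of the randomised comparison.

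**Working it through.** **Plan's own figures.** The article gives no standard deviation, score difference or baseline-to-follow-up correlation. Its sample size is built on two proportions ("P1 = HIV Prevalence in 2012 = 0.189 & P2 = HIV Prevalence in 2014 = 0.163"), so there is no planned power on the score scale to reproduce. Two of its inputs are used below: 20 patients per cluster and an ICC of 0.05. They give a design effect of 1 + (20 − 1) × 0.05 = 1.95, which the article rounds to 2.

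**Assumption.** The correlation r between baseline and follow-up score is not in the document. The range 0.3 to 0.7 is assumed, with equal variance at each visit.

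**Step 1: patient-level variance with one follow-up, relative to the follow-up score alone.**
- Follow-up score only: 1
- Change from baseline: 2(1 − r)
- Baseline as covariate (ANCOVA): 1 − r²
- ANCOVA relative to change: (1 − r²) / [2(1 − r)] = (1 + r)/2

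| r | Change | ANCOVA | Saving vs follow-up only | Saving vs change |
|---|---|---|---|---|
| 0.3 | 1.40 | 0.91 | 9% | 35% |
| 0.5 | 1.00 | 0.75 | 25% | 25% |
| 0.7 | 0.60 | 0.51 | 49% | 15% |

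For any r between 0 and 1, both 1 − r² and (1 + r)/2 are below 1. ANCOVA therefore has the smallest variance whatever r turns out to be; only the size of the gain depends on r.

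**Step 2: from patient level to trial level.** With total variance 1, the variance of a cluster mean is ICC + (1 − ICC)/m = 0.05 + 0.95/20 = 0.05 + 0.0475 = 0.0975. The within-cluster part is 0.0475/0.0975 = 49%. If baseline explains only within-cluster variation, the saving against follow-up scores at r = 0.5 falls from 25% to 0.49 × 25% = about 12%. It is larger if baseline also explains differences between clusters. The document does not allow a choice between these.

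**Step 3: conditional, the repeated-measures group main effect.** Suppose the true arm difference is 0 at baseline and d at both follow-ups. The main effect averages the three visits: (0 + d + d)/3 = 0.67d. This matters only if that term is read as the SMS effect.

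**Step 4: conditional, missed visits.** Suppose the repeated-measures ANOVA is run on complete cases, and 5% or 10% of patients miss each of the two follow-ups independently (assumed). Of 192 per group, 192 × 0.95² = 173 or 192 × 0.90² = 156 remain. A model that needs only one follow-up would lose 0.05² = 0.25% or 0.10² = 1% of patients. If the losses are instead patients who never return after baseline, neither approach recovers them.

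**The case against.** The strongest reply is that much of this depends on how a short paragraph is read.

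- **Baseline is not ignored throughout.** The Abstract defines the outcomes as differences from baseline. The matching repeated-measures term is group-by-time, which uses baseline and removes baseline imbalance. This stands: the loss there is one of efficiency, and at r = 0.8 the gain over change is only 10%. With three visits the interaction is also a 2-degree-of-freedom test, so the one-follow-up formula is only a guide.
- **The quantity compared by the t-test and one-way ANOVA is not stated.** It could be change. The objectives' comparison of mean scores at each visit points towards scores by visit but does not settle it. On either reading baseline adjustment is better; the reading decides which column of the table applies.
- **Diluted effect.** A reader might infer that the SMS effect will be shrunk to two thirds. The article never says that the group main effect will be the treatment effect, so 0.67d is a warning about one possible use.
- **Lost patients.** A reader might infer that anyone who misses a visit is dropped. The article does not say so. Its handling of missed visits may stand in a fuller document, and its sample size already allows for 10% attrition. This too is conditional.
- **Lost power.** A reader might turn the percentages into a stated loss of trial power. There is no score-scale power calculation to lose from, and the percentages are patient-level.

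What survives is that every test named for the arm effect lacks the baseline covariate, and that adding it is better for any r between 0 and 1.

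**Conclusion.** The point holds as a matter of efficiency. The article fixes t-tests, one-way ANOVA and two-way repeated-measures ANOVA for the score outcomes. None adjusts for a baseline score that is collected in any case. The patient-level saving from adjustment is 9 to 49% against follow-up scores alone and 35 to 15% against change with one follow-up, for r from 0.3 to 0.7. The saving against follow-up scores could be about half that at trial level, depending on how far baseline explains differences between clusters.

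These figures assume a continuous score, equal variances across visits and a value of r that the document does not give. The direction needs only r between 0 and 1. The dilution to 0.67d and the loss of incomplete patients remain conditional on choices that the article does not state.

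**What to change.** For the knowledge, attitude and practice scores, replace the t-test, one-way ANOVA and repeated-measures ANOVA as tests of the arm effect with one linear mixed model:

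- Outcome: the immediate and 3-month scores.
- Fixed effects: baseline score, arm, time and arm-by-time.
- Random effects: hospital/NGO and patient.
- Patients: all with at least one follow-up score.
- Inference: a small-sample correction to the degrees of freedom, because there are only about 20 clusters.

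Report the adjusted arm difference with its 95% confidence interval at each of the two follow-ups, since the Abstract does not single out either. State that the repeated-measures group main effect will not be used as the treatment effect. The random hospital/NGO term also carries into the analysis the clustering that the sample size already assumes.

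The cost is analysis wording only. No new data, visits or patients are needed, because baseline is already measured.
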